## Methods

### Study Design

The study is being conducted with a randomized waitlist control design, such that participants were randomized through Qualtrics to either begin the intervention immediately or after 8 weeks. In addition, participants were invited to participate with the goal of impacting anxiety- or cancer-related neuropathy as a primary outcome (additional discussion on this below). The goal was to have 200 people complete the 8-week survey measures in each group. Funding was originally garnered to examine anxiety as a primary outcome, with additional seed funding received through the University of Hawai’i Cancer Center to test the same design for cancer-related neuropathy. These groups will not be compared with each other, rather, each treatment group (anxiety- and cancer-related neuropathy, respectively) will be compared with each waitlist control group (anxiety- and cancer-related neuropathy).

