### Procedure

#### Recruitment

Recruitment closed for the study in July 2023. The University of Hawai’i (UH) Cancer Center is recognized by the National Cancer Institute as one of their designated cancer centers. The Hawai’i Cancer Consortium, to which all major medical centers on Oahu belong, is led by the UH Cancer Center. Recruitment efforts took place in oncology clinics, via the web, and through organized community events [31]. These included local medical centers and clinical offices, public events (eg, senior fair), and cancer organizations, such as the American Cancer Society and Stupid Cancer, via social media and newsletter unpaid advertisements.

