#### Participants

Cancer survivors experiencing anxiety- or cancer-related neuropathy who had finished primary treatment for cancer were invited to participate in the study. They were first screened and then consented via Qualtrics, where all data were collected, as well. Inclusion criteria were the same for both groups, aside from the different scales used to measure levels of anxiety or neuropathy. Inclusion criteria for both groups include a previous diagnosis of cancer, other than nonmelanoma skin cancer; completion of primary treatment for cancer; not currently practicing meditation for more than 1 hour per week; age older than 21 years; comfortable reading and writing in English; routine access to the internet; and own a smartphone or tablet. There are no exclusion criteria.

For the anxiety group, participants needed to be experiencing cancer-related anxiety, per self-report, as indicated by a score of 22 or higher on the PROMIS (Patient Reported Outcomes Measurement Information System) anxiety short form measure [32]. For the neuropathy group, participants needed to be experiencing CIPN, per self-report, as indicated by a score of 22 points or higher on the Functional Assessment of Cancer Therapy-Cognitive subscale (FACT-GOG-Ntx) CIPN items [33]. The study was powered to examine differences between groups with 200 people in each group (200 total for anxiety, 200 total for neuropathy).

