## Results

### Overview

We will conduct the primary evaluation of the intervention, comparing changes in multiple outcomes between the treatment and waitlist control groups. Participants were randomized using a simple, open-label (nonblinded) randomization procedure. The intervention was individually guided and conducted electronically. We will follow an intent-to-treat approach, in which individuals are analyzed based on their randomization groups, regardless of adherence. Adherence effects will be examined in a subsequent analysis.

To account for repeated measures, we will run a mixed (both between- and within-subjects variables) linear or logistic model for each outcome. The independent variables are the randomization group (treatment vs waitlist control), time (baseline, 8 weeks, or 16 weeks), and the group by time interaction. The interaction term tests the intervention effect. For all analyses, the assumptions of the models will be checked and remedial measures (eg, transformations and nonparametric tests) will be taken as needed. Logistic models will assess dichotomous outcomes and linear models will assess continuous outcomes. Potential confounders (adherence, age, sex, and race or ethnicity) will be included. Where possible we will run the analyses within subgroups defined by these covariates, providing information on whether the intervention was more effective in certain groups (moderator effects). If there is evidence of nonrandom missing data, such as by differential dropout between groups, we will apply multiple imputation procedures. SAS (version 9.4; SAS Institute Inc) will be used to perform all analyses.

Data collection began in 2019 and was completed in 2023. We had very differential rates of recruitment for the differing arms with reaching near the target for the anxiety arm yet not for the cancer related neuropathy arm. This, along with other outcomes of the study will be reported in a separate manuscript.

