### Power

Assuming a Bonferroni corrected (for 10 outcome measures) 2-tailed type I error rate (α) equal to .005 (0.05/10), 80% power, and 200 participants per group (400 total), a standardized difference (Cohen *d* effect size) of 0.37 will be detectable. Cohen *d* is the standardized difference and can be converted to the original units by multiplying the SD of the original variable.

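### The single detectable effect of 0.37 assumes 200 per randomised arm, but each condition was planned at 200 in total and neuropathy closed below that

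*Protocol article*

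**What the plan says.** **Planned size.** The Participants section of the protocol article states: "The study was powered to examine differences between groups with 200 people in each group (200 total for anxiety, 200 total for neuropathy". Here a group is a condition, and 200 is the total for that condition. The Study Design section says what is counted: "The goal was to have 200 people complete the 8-week survey measures in each group". It also says that the two conditions are not compared with each other. Each condition's treatment group is set against its own waitlist group.

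**Power.** The Power section uses a "2-tailed type I error rate (α) equal to .005 (0.05/10"), with "80% power, and 200 participants per group (400 total"), and concludes that a Cohen d "of 0.37 will be detectable". It gives one figure for the whole study and no separate line for either condition.

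**Recruitment.** The Recruitment section reports: "Recruitment closed for the study in July 2023". The Results overview says that recruitment ended "reaching near the target for the anxiety arm yet not for the cancer related neuropathy arm" (arm here means condition). It gives no number and leaves the details to a later paper.

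**The concern.** The word group carries two meanings. In the Participants section, two groups of 200 are two conditions. In the Power section, two groups of 200 give the 0.37 only if they are the two sides of one comparison. The study has no comparison with 400 people in it, so the quoted sensitivity belongs to neither primary question.

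The recruitment report adds to this for neuropathy. Enrolment is closed and that condition did not reach its planned 200. Anxiety participants cannot make up the difference, because arms are compared only within a condition. The Power section nevertheless follows the disclosure with an unqualified 0.37.

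What is at stake is how either primary result is judged. A reader who takes 0.37 as the effect the trial could detect would credit both comparisons with more sensitivity than they have, and the neuropathy comparison most of all.

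**Working it through.** **Inputs from the article**
- Two-sided alpha: 0.05/10 = 0.005 (Power).
- Power 80%; 200 per group, 400 total; detectable d = 0.37 (Power).
- 200 in total per condition, counted as people completing the 8-week survey (Participants; Study Design).
- Comparison: treatment against waitlist within each condition (Study Design).

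**Assumptions, not stated in the article**
- 1:1 allocation, so 200 in total means 100 per arm.
- A plain two-sample comparison of means with SD 1, with no credit for baseline or repeated measures.
- Neuropathy totals of 150, 100 and 50. The achieved number is not given, so these are illustrations only.

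**Formulas** (n = number per arm)
- Detectable effect, normal approximation: d = (z(0.9975) + z(0.80)) × √(2/n) = (2.807 + 0.842) × √(2/n) = 3.649 × √(2/n).
- Power at a given d: Φ(d/√(2/n) − 2.807).
- The noncentral t with 2n − 2 degrees of freedom gives slightly larger detectable effects. Its values are the ones quoted in the conclusions.

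**Step 1: reproduce the stated figure.** With n = 200 per arm, d = 3.649 × √(2/200) = 3.649 × 0.1 = 0.365 (noncentral t: 0.367), which rounds to 0.37. Conversely, d = 0.37 needs 195 per arm. The arithmetic in the Power section is therefore right for two arms of 200.

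**Step 2: one condition at its full planned size.** With n = 100 per arm, d = 3.649 × √(2/100) = 3.649 × 0.1414 = 0.516 (noncentral t: 0.521). Power at d = 0.37 is Φ(0.37/0.1414 − 2.807) = Φ(−0.19) = 42% (noncentral t: 41%). This holds for anxiety and neuropathy alike, before any shortfall.

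**Step 3: illustrative neuropathy totals below 200** (alpha .005, 80% power)

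| Total in condition | Per arm | d, normal | d, noncentral t | Power at 0.37, noncentral t |
|---|---|---|---|---|
| 200 (planned) | 100 | 0.516 | 0.521 | 41% |
| 150 | 75 | 0.596 | 0.604 | 28% |
| 100 | 50 | 0.730 | 0.745 | 16% |
| 50 | 25 | 1.032 | 1.076 | 6% |

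**Step 4: could baseline adjustment recover 0.37?** At 100 per arm the variance would have to shrink by the factor (0.37/0.516)² = 0.514. Adjusting for baseline multiplies the variance by 1 − ρ², so ρ would have to be √(1 − 0.514) = 0.70. The article states no such correlation, and its power statement does not use one.

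**Step 5: does the choice of alpha explain it?** At an uncorrected two-sided .05, 100 per arm detects d = 0.40. That is near 0.37, but the article states .005.

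**The case against.** The strongest reply is that nothing is concealed or miscalculated. The shortfall is disclosed immediately before the Power section. Missing a recruitment target is not an error in a plan, and achieved numbers are results, which the article assigns to another paper. The Participants statement is in the past tense and the Power statement begins from an assumption, so both can be read as records of the plan. The 0.37 follows from its stated inputs.

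Much of this stands. The planned 200 remains true as a planned size and need not be removed; the shortfall is measured against it. A fixed rule for interpreting non-significant results is ordinary matter for an analysis plan or results paper, neither of which is shown. Nothing in the article says that a null neuropathy result would be taken as proof of no benefit.

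What does not stand is the defence of 0.37 as a record of the plan. The plan was 200 per condition, and the assumption in the Power section is a different one. Even with recruitment exactly on target, 0.37 would not have been the detectable effect in either comparison under the stated alpha and power.

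The mixed model over three time points could improve precision, so the detectable effects above may be somewhat pessimistic. By how much cannot be judged without a correlation.

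**Conclusion.** The point holds in this form: the one detectable effect in the Power section fits neither comparison the trial makes. At the planned 200 per condition it is 0.52 rather than 0.37, and power at 0.37 is 41% rather than 80%. For neuropathy the true position is worse still, by an amount that cannot be determined from the article. These figures rest on a 1:1 split, alpha .005 and a simple two-sample comparison.

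Two stronger readings are tempting and should be resisted:
- A reader might infer that 0.37 fails for neuropathy because recruitment fell short. It does not: the full 200 would already have given 0.52. The main cause is the per-arm versus per-condition mismatch, which affects anxiety equally. The shortfall only adds to it.
- A reader might infer that the neuropathy comparison can detect only large effects. The achieved number is unknown, and the illustrative values of 0.60 at 150 total and 0.74 at 100 total lie below the conventional 0.8 for a large effect. Only the 50-total case, at 1.08, lies above it.

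**What to change.** In the Power section, replace the single 0.37 with one line for each condition. Compute each detectable effect from the actual number per randomised arm with 8-week data, at the stated alpha and power. If credit is taken for baseline or repeated measures, state the correlation used.

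Keep 200 per condition as the planned size. Add that neuropathy recruitment fell below it, and that the neuropathy result should be read from its estimate and 95% CI.

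The cost is a few restated figures, less favourable than 0.37, and one sentence. No new data and no further enrolment are needed.

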### Power

Assuming a Bonferroni corrected (for 10 outcome measures) 2-tailed type I error rate (α) equal to .005 (0.05/10), 80% power, and 200 participants per group (400 total), a standardized difference (Cohen *d* effect size) of 0.37 will be detectable. Cohen *d* is the standardized difference and can be converted to the original units by multiplying the SD of the original variable.

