**Methods:**

In this randomized waitlist controlled trial, cancer survivors experiencing anxiety- or cancer-related neuropathy (200 for neuropathy and 200 for anxiety) and who had finished primary cancer treatment were invited to participate. Data were collected at 3 time points regardless of randomization condition: baseline, 8 weeks, and 16 weeks. Both face-to-face and web-based recruitment strategies were used. The trial was opened for 2 separate primary outcomes (anxiety- or cancer-related neuropathy). The goal was not to compare these groups but to compare treatment and waitlist groups for each condition. In addition to evaluating the impact of mobile mindfulness on reported anxiety- or cancer-related neuropathy, other pain, fatigue, trauma, sleep, and satisfaction with the Mindfulness Coach app will also be assessed.

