Mindfulness Coach, an iOS- and Android-based mobile app, is designed to deliver a mobile mindfulness training course designed by researchers from the US Department of Veterans Affairs [21,28]. The senior author of this paper, ER, was part of the team that developed the most recent version of the app. Initially developed among other mobile apps in collaboration with the US Department of Defense [28], Mindfulness Coach is freely available to the general public for both iOS and Android operating systems. A recent study exploring the effects of the app among the general population found that use of the Mindfulness Coach app was feasible, and increased use was strongly correlated with an increase in scores measuring mindfulness characteristics including observing, describing, acting with awareness, nonreactivity to inner experience, and nonjudging of inner experience, as measured by the Five-Facet Mindfulness Questionnaire Short Form (FFMQ-SF) [21,29]. Although mobile health is increasingly being used in research and clinical settings, a recent systematic review and meta-analysis concluded that there is still inconclusive evidence due to small nonsubstantial effects of interventions, as well as concerns regarding study quality [30].

Given the persistent effects of diagnosis and treatment and the limitations of in-person offerings in most places, the Mobile Mindfulness Study was conducted to test the impact on anxiety- and cancer-related neuropathy after 8 weeks of use of the Mindfulness Coach mobile app. The study contains the following secondary aims: evaluate the impact of mobile mindfulness on general pain, fatigue, trauma, and sleep, in addition to evaluating the satisfaction with the Mindfulness Coach mobile app. The goal of this paper is to describe the study design.

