#### Anxiety Group

Potential participants were screened with the PROMIS anxiety short form measure, an 8-item measure assessing anxiety on a Likert-type scale, with options ranging from “never” to “always” [32]. Pain is measured with the Pain Intensity Enjoyment of Life General Activity Scale, a 3-item measure assessing pain intensity, interference with general activity, and interference with enjoyment of life, with response options ranging from a 0-10 scale, with 0 being “no pain” or “does not interfere” and 10 being “pain as bad as you can imagine” or “completely interferes” [34]. Sleep-related impairment is measured using the PROMIS sleep-related impairment short form, an 8-item measure assessing sleep disturbance and sleep-related impairment [35]. Fatigue is measured with the brief fatigue inventory, a 9-item measure to rate fatigue on a 0-10 scale, with 0 being “no fatigue” or “does not interfere” and 10 being “as bad as you can imagine” or “completely interferes” [36]. Anxiety is measured with the General Anxiety Disorder 7-item measure of anxiety on a 5-point Likert-type scale [37]. Depression is measured with the Patient Health Questionnaire-9, a 9-item measure using 4 response options to assess depressive symptoms and behaviors [38]. PTSD is measured using the PTSD Checklist for DSM-5, a 20-item measure that assesses the 20 *Diagnostic and Statistical Manual of Mental Disorder* symptoms of PTSD [39]. Mindfulness is measured with the FFMQ, a 39-item measure of the 5 facets of mindfulness (observing, describing, acting with awareness, nonjudging of inner experience, and nonreactivity to inner experience), with answer options on a 1-5 scale ranging from “never or rarely true” to “very often or always true” [29]. For the follow-up assessments, the demographic questions are removed. A question regarding how much they have been practicing mindfulness (all groups), and a question about satisfaction with the intervention (for the intervention groups) are added.

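### The power statement charges a 10-outcome Bonferroni correction (alpha .005) with no separate level for each condition's primary outcome, and does not identify the 10 outcomes

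*Protocol article*

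**What the plan says.** All references are to the protocol article.

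- **Hierarchy.** The Methods part of the abstract states: "The trial was opened for 2 separate primary outcomes (anxiety- or cancer-related neuropathy". Study Design adds that the two conditions are not compared with each other; each is a treatment-versus-waitlist comparison of its own. The end of the Introduction sets a second tier, beginning "The study contains the following secondary aims", which covers general pain, fatigue, trauma, sleep and satisfaction with the app. Depression, mindfulness and quality of life are measured but placed in neither tier.
- **Analysis.** The Overview under Results describes the primary evaluation as "comparing changes in multiple outcomes between the treatment and waitlist control groups", with one mixed model per outcome. It states no significance level.
- **Power.** The only alpha in the article is in the Power section: "Assuming a Bonferroni corrected (for 10 outcome measures) 2-tailed type I error rate" of .005 (0.05/10), with "80% power, and 200 participants per group (400 total"). The result is that "a standardized difference (Cohen *d* effect size) of 0.37 will be detectable". The 10 measures are not named.
- **Instruments.** Anxiety Group names eight. PROMIS anxiety is described there as the screener, while "Anxiety is measured with the General Anxiety Disorder 7-item measure of anxiety". Neuropathy Group names five. No scale is designated as the primary one in the anxiety condition.

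**The concern.** A single prespecified primary outcome in a separately analysed comparison needs no correction for secondary outcomes. The article declares such a hierarchy and then powers the trial as if ten outcomes stood on the same footing. If .005 becomes the test level, the question for which each condition was opened is held to a tenth of the usual error rate in order to protect claims the article itself ranks lower.

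The divisor also cannot be checked. The same 10 is applied to two conditions with different instrument sets, and the article does not say which measures make it up. Since no anxiety scale is named as primary, a reader cannot tell which single test would be entitled to the full .05.

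Recruitment is closed and the Overview reports that the neuropathy condition did not come near its target, so power given up through alpha cannot be recovered by enrolling more participants.

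**Working it through.** **Inputs.** Two-sided alpha .05/10 = .005, 80% power, 200 per group and d = 0.37 (Power section). 200 in total per condition (Participants), hence about 100 per arm if allocation is 1:1; the ratio is not stated, so this is an assumption.

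**Formulas** (two-sample comparison of means, normal approximation):

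- detectable d = (z(1−α/2) + z(0.80)) × √(2/n per arm)
- power at d = Φ(d/√(2/n) − z(1−α/2))

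with z(0.80) = 0.842, z(0.9975) = 2.807 and z(0.975) = 1.960.

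**Step 1: reproduce the stated figure.** With n = 200 per arm, √(2/200) = 0.100, so d = (2.807 + 0.842) × 0.100 = 0.365. The noncentral t gives 0.367. Both round to 0.37, so the arithmetic is right for its inputs.

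**Step 2: change alpha only.** With n = 100 per arm, √(2/100) = 0.1414.

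| n per arm | alpha | detectable d (normal / t) | power at d = 0.37 (normal / t) |
|---|---|---|---|
| 200 | .005 | 0.365 / 0.367 | 81.4% / 80.9% |
| 200 | .05 | 0.280 / 0.281 | 95.9% / 95.8% |
| 100 | .005 | 0.516 / 0.521 | 42.4% / 41.4% |
| 100 | .05 | 0.396 / 0.398 | 74.4% / 74.0% |

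At either sample size the tenfold correction raises the detectable effect by about 30% (3.649/2.802 = 1.30).

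**Step 3: count the outcomes.**

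- *Anxiety condition*, eight instruments: PROMIS anxiety, the three-item pain scale, PROMIS sleep-related impairment, Brief Fatigue Inventory, GAD-7, PHQ-9, the PTSD checklist and the FFMQ. Quality of life, which Baseline and Follow-Up Assessments says is asked in both conditions, makes 9. The follow-up question on amount of practice makes 10, and the satisfaction question 11.
- *Neuropathy condition*, five instruments: the 11 neuropathy items, the 27 FACT items, PROMIS anxiety, Brief Fatigue Inventory and the short-form McGill. The practice and satisfaction questions make 7.

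Satisfaction is asked only of the intervention groups, so it cannot be a treatment-versus-waitlist outcome. Amount of practice is closer to exposure than to outcome.

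**Step 4: effect of a different divisor.** With 200 per arm (normal approximation), a divisor of 5, 8 or 9 gives a detectable d of 0.342, 0.358 or 0.361, against 0.365 for 10. The exact divisor matters little. What matters is whether the primary outcome is in the family at all.

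**The case against.** **The .005 is an assumption for power, not a test rule.** This stands. The figure follows the word assuming, and the Overview gives no test-level alpha. A reader might infer that every outcome will be tested at .005; the article does not say so, and the operative rule may be in a document not shown. The loss of power is therefore conditional on the correction being carried into the analysis.

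**The number 10 may be right.** A reader might infer that neither condition has 10 outcomes and that the divisor is an error. The article does not support that. Anxiety reaches 10 with quality of life and the practice question. Neuropathy could also reach 10 if subscales are counted: four well-being domains, the neuropathy items, PROMIS anxiety, fatigue, sensory and affective pain, and practice (4 + 1 + 1 + 1 + 2 + 1 = 10). These are possible counts, not a stated list. What can be said is that the 10 are unidentified and do not match the named instruments in either condition without additions or splitting.

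**The hierarchy is incomplete.** Also true. It is too much to say that everything except the primary is called secondary. The Overview's description of a multi-outcome primary evaluation is compatible with a correction across outcomes, and while no anxiety scale is named, some correction is defensible. This shows that the passages need reconciling; it does not reconcile them.

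**The largest loss comes from another defect.** The 42% against 74% comparison needs 100 per arm, whereas the Power section uses 200. At 200 per arm the primary still has about 81% power at d = 0.37 under the correction. The conflict between 200 per arm and 200 per condition is separate and should not be credited to alpha.

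**No validity error is shown.** Correct: the correction is conservative. Relaxing the only published alpha after data collection in an open-label trial could also look opportunistic, which is a real cost of the remedy.

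**Conclusion.** The concern holds as an inconsistency that costs power. The article gives each separately analysed condition one primary construct and a set of secondary aims, but its only alpha is .05/10, with no level reserved for the primary and no list of the ten.

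If .005 is used for the primary test, the detectable d at 80% power is 0.37 instead of 0.28 with 200 per arm, or 0.52 instead of 0.40 with about 100 per arm. These figures assume a simple two-sample comparison, 1:1 allocation for the smaller size, and full recruitment, which the neuropathy condition did not reach.

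Changing alpha does not by itself restore the power statement: at 100 per arm and two-sided .05, power at d = 0.37 is about 74%. Type I error is not inflated by the plan as written.

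**What to change.** Before any outcome is examined by arm, and with a dated record:

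1. Name one primary scale per condition. For anxiety the sponsor chooses between GAD-7, the scale that Anxiety Group assigns to measuring anxiety, and PROMIS anxiety, which defines eligibility. For neuropathy use the 11-item FACT-GOG-Ntx score.
2. Test that scale at 8 weeks at two-sided .05 within its condition.
3. List each condition's secondary treatment-versus-waitlist outcomes, giving a rank to depression, mindfulness and quality of life, and test them as a separate family with Holm at .05 using that condition's own count.
4. Align the Overview's description of the primary evaluation with this hierarchy.
5. Restate the power paragraph at .05 for the primary, using the per-arm number that applies to one condition. With 100 per arm the detectable d is 0.40.

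The cost is wording in the analysis plan and power section, with no new participants. There are two downsides. Family-wise error is controlled separately for the primary and for the secondary family, not jointly over all outcomes. The change also comes after data collection, so the report must disclose it, give its date and state that outcomes had not been examined by arm.

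### The only multiplicity level stated is Bonferroni .005; if it becomes the testing threshold, Holm's step-down at the same familywise 5% would reject at least as much

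*Protocol article*

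**What the plan says.** In the Protocol article, the Power section sets out the sizing assumptions: "Assuming a Bonferroni corrected (for 10 outcome measures) 2-tailed type I error rate", with the level and power given as "2-tailed type I error rate (α) equal to .005 (0.05/10), 80% power". The sample size used is "200 participants per group (400 total", and the result is a Cohen d "effect size) of 0.37 will be detectable".

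The analysis text is in the Overview under Results. It describes "comparing changes in multiple outcomes between the treatment and waitlist control groups", with a mixed linear or logistic model for each outcome and the group-by-time interaction as the test of the intervention. It gives no significance threshold and no multiplicity procedure.

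On size, the Participants section gives "200 total for anxiety, 200 total for neuropathy". Of the two conditions, the Study Design section says "These groups will not be compared with each other". Each is analysed as treatment against waitlist within the condition.

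**The concern.** A reader looking for the decision rule finds only .005, and would naturally apply it to every outcome. Used that way, the rule is single-step Bonferroni: each outcome faces 0.05/10 whatever happens to the others. Holm's procedure faces 0.05/10 only at the first step. After each rejection the next smallest p-value is compared with a larger fraction of 0.05. It protects the familywise 5% just as strictly, without any assumption about correlation, and cannot lose a rejection that Bonferroni would make.

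At stake is power for the second and later outcomes. That matters most if the app shifts several symptom domains. The anxiety battery, for example, covers anxiety, depression, PTSD, sleep-related impairment, fatigue, pain and mindfulness.

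**Working it through.** **Inputs.** Family of 10 outcomes, two-sided .005 per outcome, 80% power, 200 per group and d = 0.37 (all from Power); 200 in total per condition (Participants). Assumptions: 1:1 allocation, so about 100 per arm per condition (the ratio is not stated); a true d of 0.4 for each responding outcome; a common correlation between outcomes; and 1, 3, 5 or 10 outcomes truly responding.

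**Step 1: the plan's own figure.** The level is 0.05/10 = .005. The detectable difference is d = (z₀.₉₉₇₅ + z₀.₈₀) × √(2/n) = (2.807 + 0.842) × √(2/200) = 0.365. A noncentral t calculation gives 0.367. Both round to the stated 0.37, so the figure reproduces on its own inputs.

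**Step 2: validity of Bonferroni.** With ten independent true nulls, the familywise error is 1 − (1 − 0.005)¹⁰ = 4.89%, within 5%.

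**Step 3: Holm's thresholds.** Order the p-values and compare them with 0.05/10 = .005, 0.05/9 = .0056, 0.05/8 = .00625, and so on up to 0.05/1 = .05, stopping at the first failure. The first threshold is the same as Bonferroni's. Two things follow. The chance of at least one rejection is identical under both rules, and .005 remains the right worst-case level for sizing.

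**Step 4: Bonferroni power at about 100 per arm, d = 0.4.** Φ(0.4 × √(100/2) − 2.807) = Φ(2.828 − 2.807) = Φ(0.021) = 51%.

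**Step 5: Holm power in the same setting.** By simulation: ten two-sided z tests, mean d × √(100/2) for responding outcomes, correlations of 0.3 and 0.5.

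| Outcomes truly responding (of 10) | Bonferroni, per affected outcome | Holm, per affected outcome |
|---|---|---|
| 1 | 51% | 51% |
| 3 | 51% | 52% |
| 5 | 51% | 54% |
| 10 | 51% | 62% |

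No simulated trial had a Bonferroni rejection that Holm missed. In expected extra true findings per condition, five responders give 5 × (0.54 − 0.51) = 0.15, and ten give 10 × (0.62 − 0.51) = 1.1.

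**Step 6: sensitivity.** At d = 0.37 and 100 per arm, per-outcome power is about 42% under Bonferroni and 42% to 52% under Holm, depending on how many respond. At d = 0.37 and the Power section's 200 per arm, Bonferroni gives about 81% to 82%. Holm gives 81.5% (one responding), 83% (three), 84% to 85% (five) and 91% to 94% (all ten). Its familywise error in these runs was at most about 4.8%.

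**The case against.** The strongest objection is that .005 appears only as an assumption for sizing. The Overview sets no threshold, and the choice between a single-step and a step-down adjustment is commonly left to a statistical analysis plan, which is not shown. This stands. A reader might infer that the trial has committed to plain Bonferroni tests and is giving power away. The documents do not show that, so the point is conditional on .005 being carried into the analysis. If the analysis plan already names Holm or a hierarchy, the point falls away.

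A reader might also infer that the power figure is wrong because it uses Bonferroni. It is not, on this ground: Holm starts at the same .005.

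Nor is the gain free, or always large. Single-step Bonferroni yields simple simultaneous confidence intervals and Holm does not. The gain of about 11 points needs all ten outcomes to respond, and the article's own background gives reason for doubt: it cites a meditation-app study that improved depression and anxiety but not, to any substantial degree, sleep disturbance.

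It is tempting to argue that related scales are where step-down testing gains most. The gain comes from many outcomes being truly affected, and correlation as such does not produce it. With all ten responding at 200 per arm and d = 0.37, the gain is about 12 points at correlation 0 and about 9 at 0.5.

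Finally, the ten-outcome, 100-per-arm setting fits the anxiety condition better than the neuropathy condition. The latter has a different battery, and the Overview says its recruitment fell short of target.

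**Conclusion.** The point holds conditionally, as an efficiency recommendation. The document's only stated multiplicity control is Bonferroni at .005. That level is valid and is the correct worst-case basis for sizing. As a fixed testing threshold it is dominated by Holm at the same familywise 5%: Holm never rejects less, under any dependence.

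The benefit ranges from nothing when one outcome responds, through roughly 1 to 3 points per affected outcome with three to five responding, to about 11 points if all ten do. There is no change in the chance of finding at least one effect. That Holm never rejects less is a general result and needs none of the assumptions above. The sizes rest on 1:1 allocation, about 100 per arm, d = 0.4 and a family of ten.

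Holm does not resolve the separate mismatch between the Power section's 200 per group and the 200 in total per condition given under Participants.

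**What to change.** Add one sentence to the analysis text or the analysis plan: within each condition, the adjusted outcome family is tested by Holm's step-down procedure at familywise 5%, with Holm-adjusted p-values reported and unadjusted 95% confidence intervals beside them. Leave .005 as the level used for sizing, described as the worst case.

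The sentence must be dated, with a statement that it was fixed before any outcome was compared by arm. Data collection finished in 2023 and the trial is open-label, so an undated move to a less strict rule could look driven by results.

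No new data, participants or outcomes are needed. The costs are that documentation and the loss of simple simultaneous confidence intervals.
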